## Secondary outcomes

### Motor-evoked potential (MEP)

The study will employ single-pulse transcranial magnetic stimulation (sTMS, Xiang Yu Medical; China) to the primary motor cortex (M1 area) of the hand region. This technique will measure motor-evoked potential (MEP) in the first dorsal interosseous muscle via surface electrodes. MEP amplitude, latency, resting motor threshold (RMT), active motor threshold (AMT), and central motor conduction time (CMCT) will be evaluated as indicators of corticospinal tract function. Subjects will be seated comfortably with their head and arm relaxed. The TMS coil will be placed 5 cm lateral to the vertex, aligning at a 45° angle from the brain midline with the handle pointing backwards. The location yielding consistently maximal MEP responses will be identified as the “motor hotspot” [27]. The magnetic stimulus intensity will be set at 20% above the MEP threshold. The TMS operator will adjust the magnetic cortical stimulus intensity to elicit MEPs of peak-to-peak amplitude 1 mV on average [28]. Five sequential stimulations will be administered at each intensity, and the average of the resulting five MEP traces will be used for data analysis. Latency will be reported as mean ± SD, while amplitude will be represented by the median due to data distribution skewness.

CMCT indicates the time it takes for a signal to travel from the motor cortex to spinal motor neurons. To measure CMCT, we will use spinal magnetic stimulation. After cortical stimulation, each participant will undergo cervical stimulation. The coil will be placed above the C7 spinous process, 2 cm lateral to the midline, aiming to activate cervical nerve roots at the intervertebral foramina. Participants will experience an MEP with a latency time from cortical magnetic stimulation of the first dorsal interosseous muscle. They will also experience an MEP with a different latency time due to cervical magnetic stimulation of the same muscle (peripheral motor conduction time). The difference between these two latency times provides the CMCT value.

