**Methods:**

This trial is a prospective, randomized controlled, double-blind study. All enrolled patients were randomly assigned to two groups. The experimental group received intervention through 40-Hz visual-auditory stimulation, while the control group underwent intervention with randomly matched visual-auditory stimulation frequencies. The primary efficacy endpoint is the change in motor function. Secondary efficacy endpoints include motor-evoked potentials, cerebral hemodynamic changes, neural network connectivity, and alterations in synaptic-related genes. Safety evaluation included major adverse events, all-cause mortality, and photosensitive epilepsy. Assessments will be conducted at baseline, after a 14-day treatment period, and during subsequent follow-up visits (at 3 and 6 months) post-treatment. The differences between the two groups will be compared.

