### Eligibility criteria {10}

#### Inclusion criteria

Age ≥ 40 years.Acute anterior circulation ischemic stroke patients meeting the following criteria:(2.1)Impaired contralateral limb motor function.(2.2)Paralysis of the affected limb with muscle strength rated at levels I–IV according to the Brunnstrom staging.Onset of symptoms within 1 week.Sign an informed consent form.

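### MEP amplitude is a listed secondary measure, but two unreconciled stimulus-intensity rules are given, and re-titrating to 1 mV at each visit would largely remove its between-group contrast

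*Protocol article*

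**What the plan says.** The Abstract (Methods) makes MEPs a secondary efficacy domain: "Secondary efficacy endpoints include motor-evoked potentials, cerebral hemodynamic changes, neural network connectivity, and alterations in synaptic-related genes". The section Motor-evoked potential (MEP) names five measures: "MEP amplitude, latency, resting motor threshold (RMT), active motor threshold (AMT), and central motor conduction time (CMCT) will be evaluated". Outcomes {12} schedules TMS before the intervention, at 2 weeks, and at 3 and 6 months.

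The MEP section then sets the stimulus intensity twice, in adjacent sentences. The first is a rule relative to threshold: "The magnetic stimulus intensity will be set at 20% above the MEP threshold". The second, which follows it directly, is instead a rule that aims at a response size: "The TMS operator will adjust the magnetic cortical stimulus intensity to elicit MEPs of peak-to-peak amplitude 1 mV on average".

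The next sentence covers pulses and averaging: "Five sequential stimulations will be administered at each intensity, and the average of the resulting five MEP traces will be used for data analysis". The paragraph ends by saying that "amplitude will be represented by the median due to data distribution skewness". It does not say which intensity serves which of the five measures, or whether an intensity found at one visit is kept at the next.

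**The concern.** The two rules do opposite things. Under the threshold rule, intensity is pinned to the patient's threshold and amplitude is the free quantity, so amplitude can carry a treatment effect. Under the 1 mV rule, amplitude is pinned and intensity is the free quantity. An outcome that the operator adjusts to a target before recording it cannot say much about treatment.

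At stake is one of the five MEP measures. A site following the second sentence at every visit would collect amplitudes close to 1 mV in both arms and could report no difference when excitability had in fact changed. The informative number, the stimulator output needed to reach 1 mV, is not among the listed outcomes.

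**Working it through.** **Plan's own figure.** The document gives no figure for MEP amplitude. Its only design figure is the sample size for the Fugl-Meyer outcome, used here only for the group size. A two-sided t test with effect size 0.995, alpha 0.05 and 28 per group has noncentrality 0.995 × √(28/2) = 3.72 and power 0.955. The stated 28 per group therefore reproduces (the document does not state sidedness; one-sided would need 23). This has no bearing on the point.

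**Step 1: the two rules side by side.** Let A(s) be a patient's expected amplitude at intensity s, let T be the threshold, and suppose treatment multiplies amplitude by g.

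| | Threshold rule | 1 mV rule, repeated each visit |
|---|---|---|
| Intensity used | 1.2 × T | s* such that expected amplitude = 1 mV |
| Expected amplitude, control | A(1.2T) | 1 mV |
| Expected amplitude, treated | g × A(1.2T) | 1 mV |
| Ratio, treated to control | g | 1 |
| Where the effect appears | amplitude | s* (not a listed outcome) |

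One intensity cannot in general be both 1.2 × T and s*. The loss of contrast in the right-hand column follows from the rule itself and needs no assumption about variance. It does require that the patient has an MEP that can be brought to 1 mV.

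**Step 2: size, as an illustration.** Assumed, not in the documents: log-amplitude SD 0.7 between patients and 0.5 between pulses; every patient has an MEP; titration is itself based on five pulses; arms compared by a rank test. From the documents: 5 pulses averaged, 28 per group. Results of 2,000 simulated trials per cell:

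| True gain g | Setting | Median ratio found | Rejection rate |
|---|---|---|---|
| 1.5 | 20% over threshold | 1.51 | 51% |
| 1.5 | titrated to 1 mV | 1.00 | 5% |
| 2.0 | 20% over threshold | 1.99 | 92% |
| 2.0 | titrated to 1 mV | 0.99 | 5% |

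Hand check of the threshold rows: SD of a patient's log mean = √(0.7² + 0.5²/5) = √0.54 = 0.735.

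- g = 1.5: ln 1.5 / 0.735 = 0.552; 0.552 × √14 = 2.07; Φ(2.07 − 1.96) ≈ 0.54.
- g = 2: ln 2 / 0.735 = 0.943; 0.943 × √14 = 3.53; Φ(3.53 − 1.96) ≈ 0.94.

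Both are slightly above the simulated values, as expected when a normal approximation is set against a rank test. The threshold-row percentages move with the assumed SDs. The titrated rows stay near the 5% significance level.

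**Step 3: internal consistency.** Summarising amplitude by its median because of skewness fits an amplitude that is free to vary better than one titrated to a common target. The paragraph thus leans towards the threshold setting for amplitude without saying so.

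**Step 4: the other MEP measures.** Resting and active motor thresholds are intensities in their own right and are untouched. Latency and CMCT are not fixed by a 1 mV target, although the intensity that applies to them is also unstated.

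**The case against.** The strongest reply is that the rules need not conflict. The sentence on five stimulations speaks of each intensity, which suggests more than one setting, so the two sentences may describe separate settings for separate purposes. This stands as far as it goes: a strict contradiction is not proven. But an unassigned pair of settings still leaves the condition for measuring amplitude undefined, and one candidate defeats the measure.

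A second reply is that the loss of contrast is conditional. It needs the titration to be repeated at each visit and amplitude to be read from it, and the text states neither. That also stands. Amplitude stays informative if recorded at the threshold setting, or if a 1 mV intensity found at baseline is held later. It would therefore be too strong to say that amplitude works only at an intensity set relative to threshold.

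A third concerns absent responses. A reader might infer that power is about 5% for any true effect. The documents do not support that. Eligibility is "muscle strength rated at levels I–IV according to the Brunnstrom staging", so some patients may have no MEP. They cannot be titrated, and a treatment that restored responses could still show. How absent responses are scored can be left to the analysis plan, and Statistical methods {20a} already provides a rank test for non-normal data, so neither is pressed here.

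Finally, a reader might infer that the main mechanistic endpoint is lost, or that latency and CMCT are compromised because intensity differs between patients and visits. The protocol does not rank amplitude above the other four measures. Intensity would also differ between patients under the threshold rule, so the latency and CMCT argument does not separate the two.

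**Conclusion.** The point holds in conditional form. The protocol gives two intensity rules for a listed secondary measure and reconciles them nowhere. If the 1 mV titration is repeated at each assessment and amplitude is taken from it, the between-group amplitude contrast among patients with a recordable MEP is close to nil. In the illustration, power for a 2-fold gain falls from about 92% to about 5%; those percentages rest on assumed variances, whereas the loss of contrast does not.

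The reach is limited to amplitude, one of five measures in one secondary domain. The documents do not support reading this as amplitude being fixed by design in all circumstances, or as the trial being unable to detect corticospinal change: the thresholds remain usable, and the primary outcome and sample size are untouched. It should be corrected, because a stated rule, followed literally, defeats a stated measure.

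**What to change.** In the MEP section, state for each of the five measures which intensity applies and whether it is re-determined at each visit or held from baseline. Take amplitude from the threshold-based setting already in the text, or from a baseline intensity held at later visits, and not from a setting re-titrated to 1 mV. If the 1 mV setting is kept, name the stimulator intensity needed to reach 1 mV as the outcome in place of amplitude.

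The cost is a few sentences of protocol wording and an instruction to the TMS operator; equipment, visits and sample size stay the same. Trial status reports 2 patients included, so on that status nearly all recordings could follow a single rule. The rule used for those patients' recordings should be documented.

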### CT perfusion (CTP)

Cerebral hemodynamic changes will be assessed using CTP in cerebral blood flow before and after the intervention. The imaging examination utilized a Siemens SOMATOM Force 960 + model with a 320-row spiral scanner. Patients underwent CT plain scans initially, followed by cerebral perfusion imaging using dynamic perfusion mode. The scan parameters were set as follows: collimation width of 40 mm, tube voltage of 120 kV, tube current–time product of 320 m As, gantry rotation speed of 0.35 s per rotation, pitch of 1.2375, with 20 samples (each machine movement corresponds to two samples), a sampling interval of 1.5 s, and a scan length of 105 mm. After selecting the appropriate range, the MALLINCKRODT high-pressure injector was used for intravenous injection through the antecubital median vein. Lohexol injection (370 mg I/ml) at a rate of 5 ml/s, 50 ml in total, was administered, and the scan continued for 60 s, encompassing 20 cycles and yielding 640 slices. Upon completion of the scan, the images were automatically transferred to the United Imaging AI post-processing workstation (uai_pacs). All scan data were transferred to the uai_pacs post-processing workstation, and the Stroke Protocol within the CT Brain Perfusion Analysis software was employed for processing and analysis. The software automatically generated pseudo-color maps of cerebral perfusion based on the maximum lesion level for assessment. The regions of interest included the core infarction zone and the ischemic penumbra. The software automatically matched the mirrored zones on the healthy side, obtaining related data and pseudo-color maps, encompassing cerebral blood flow (CBF), cerebral blood volume (CBV), mean transit time (MTT), time to peak (TTP), ischemic penumbra (IP) volume, and other parameters related to perfusion, thereby providing perfusion color maps.

### Functional connectivity by magnetic resonance imaging (MRI)

We will use a 3-T MRI scanner (Siemens Skyra, Erlangen, Germany), along with a circular surface coil to investigate changes in the brain. This will include evaluations of gray matter density, cortical thickness, subcortical nuclei volumes, and functional connectivity. Each participant will undergo an MRI scan lasting approximately 25 min. During the scan, they will have their eyes closed and extra padding will be placed around their ears to reduce noise interference. We will analyze changes in neural network connectivity using human connectomics. By integrating intelligent imaging technology with multimodal imaging data, including T1, DTI, and BOLD functional MRI, we can compare alterations in brain fiber connectivity patterns and changes in brain functional regions before and after treatment. This approach allows us to visualize and quantify functional connections between brain regions, alterations in the number of nerve fiber bundles, changes in the direction of nerve fiber bundle pathways, and changes in the volume of functionally abnormal regions.

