### Sample size {14}

The sample size calculation was conducted using G*power software (v3.1.9.2). The effect size of this study was estimated from a study conducted by Kaux et al. [29] who investigated the effects of transcranial direct current stimulation associated with physical therapy in acute stroke patients evaluated by the upper extremity section of the Fugl-Meyer Test, which was determined to be 0.995. The experiment employs a 1:1 simple randomization, n1 = n2. According to a prior difference between two independent means analysis *t* test, with a power of 0.95 and an error probability of 0.05, we applied these values to compute a sample size of *n* = 28. Accounting for a 10% attrition rate, we determined that each group should comprise 31 participants, yielding a total of 62 stroke patients included in the study. It is important to note that all enrolled patients received clinical medications and conventional rehabilitation treatments that were generally uniform.

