Preliminary experiments have demonstrated that 40-Hz visual-auditory stimulation can effectively improve motor function in stroke-afflicted mice. The underlying mechanism involves the restructuring of the brain’s neural network. The brain’s neural network comprises functional networks, reflecting the brain’s activity during rest or various states, and structural networks, represented by neural fibers within the brain. In 2016, the Human Connectome Project (HCP), funded by the National Institutes of Health (NIH) in the USA, established the Human Connectome Project Multimodal Parcellation (HCP-MMP1) [32]. This achievement produced a neural map that integrates both brain anatomical structure and brain function.

In previous research, our team utilized advanced neuroimaging techniques and, following the HCP parcellation method, integrated structural and functional neural networks to create multimodal fusion images that depict brain functionality. This approach combines structural, functional, and connectivity patterns, allowing for a more precise and personalized analysis of changes in brain neural networks. It is important to note that endogenous neural repair mechanisms are initiated within hours after a stroke occurs, reaching their peak at around 10 weeks and then gradually slowing down, eventually entering a plateau phase after 3 months [33]. This underscores the critical importance of the acute-phase post-stroke period for neural function protection and remodeling.

Based on this, our project aims to prospectively include patients with post-stroke upper limb motor impairment. We will employ 40-Hz visual-auditory stimulation to induce gamma oscillations and explore its effects on improving limb function. Simultaneously, we will investigate evidence of enhanced neuroplasticity within the brain’s neural circuits, connectivity, and cerebral blood flow. This approach will help us unravel the relationship between gamma oscillations and the remodeling of the brain’s neural networks. This non-invasive neuromodulation method, the 40-Hz visual-auditory stimulation, will provide a theoretical foundation for its application in acute-phase post-stroke upper limb rehabilitation. Furthermore, it will pave the way for innovative approaches in the large-scale clinical application of this neuromodulation method in the field of stroke recovery.

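### The MRI section names a single circular surface coil for whole-brain volumes and connectivity, which would measure deep and distant regions unevenly; name a whole-head receive coil and hold it constant.

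*Protocol article*

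**What the plan says.** In the protocol article, under Secondary outcomes, Functional connectivity by magnetic resonance imaging (MRI), a 3-T scanner is to be used "along with a circular surface coil to investigate changes in the brain". The next sentence lists the measures: "evaluations of gray matter density, cortical thickness, subcortical nuclei volumes, and functional connectivity". The section continues "We will analyze changes in neural network connectivity using human connectomics" and draws on "multimodal imaging data, including T1, DTI, and BOLD functional MRI", including the number and direction of fiber bundles.

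The Abstract gives the measure its role: "Secondary efficacy endpoints include motor-evoked potentials, cerebral hemodynamic changes, neural network connectivity". Outcomes {12} schedules MRI before the intervention and at three later visits. The Discussion describes the team's earlier work as "following the HCP parcellation method, integrated structural and functional neural networks", which points to a network-wide analysis. Section {18a} says that all imaging is done on one machine.

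The article mentions no head coil or multi-channel array. It does not give the surface coil's size, number of elements or position.

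**The concern.** The listed measures compare or combine signal from cortex, deep nuclei and both hemispheres. A single circular loop is most sensitive close to the patch of scalp on which it lies, so the stated hardware does not match the stated measures.

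This differs from a detail left to a fuller document. The article positively names a coil, in the singular, and the coil it names suits the purpose poorly.

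Two things are at stake. Within a scan, deep and distant regions would be measured with less signal than cortex near the coil. Between scans, a change in coil position shifts the sensitivity profile, and that shift enters the within-patient change that the endpoint reports. Keeping one machine, as {18a} does, fixes neither the coil nor its placement.

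**Working it through.** The article gives no figure for the coil, so there is none to reproduce. Its one reproducible design figure is the sample size: "which was determined to be 0.995" as effect size, "with a power of 0.95 and an error probability of 0.05". A two-sided two-sample t test with the noncentral t distribution returns 28 per group (power 0.955), as stated. It rests on the upper-limb Fugl-Meyer score and does not involve the MRI.

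**Inputs for the coil check, all assumed.** One loop of radius R, sensitivity taken on its axis at depth z. Nearby cortex is at 2 cm, deep nuclei at 7 cm and the opposite hemisphere at 13 cm. The last depth applies only if the coil lies on one side of the head, which the article does not say.

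**Formula.** For fixed R, sensitivity is proportional to R²/(R²+z²)^1.5. Relative to 2 cm this becomes

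s(z)/s(2) = [(R²+4)/(R²+z²)]^1.5

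| R | 7 cm | 13 cm |
|---|---|---|
| 5 cm | (29/74)^1.5 = 0.245 | (29/194)^1.5 = 0.058 |
| 7 cm | (53/98)^1.5 = 0.398 | (53/218)^1.5 = 0.120 |
| 10 cm | (104/149)^1.5 = 0.583 | (104/269)^1.5 = 0.240 |

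For radii of 5 to 10 cm the range is therefore about 25-58% at 7 cm and 6-24% at 13 cm. The latter is a loss of 1/0.240 = 4.2-fold to 1/0.058 = 17-fold.

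**Sensitivity to the radius.** A smaller loop does worse: R = 3 cm gives (13/58)^1.5 = 0.106 at 7 cm and (13/178)^1.5 = 0.020 at 13 cm. Sensitivity falls with depth at every radius tried. How much it falls depends on a radius and a position that the article does not state.

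**The case against.** The strongest reply is that the phrase may be loose wording for a head array built from circular elements. The article cannot settle this. If so, the images are sound and only the text is wrong, but the text still needs correcting because it misdescribes the acquisition.

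A reader might go further and infer that deep structures cannot be measured, or would be lost in noise. The documents do not support that. The calculation is a relative profile of an idealised loop. It has no baseline signal-to-noise, voxel size, sequence or noise model, and the article supplies none. With a 10 cm loop the deep nuclei keep more than half of the cortical sensitivity. The 13 cm figure needs one-sided placement.

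A reader might also infer that the connectivity question could not be answered at all. Outcomes {12} assigns network connectivity to EEG as well as MRI. EEG is not a full substitute, since its own section describes only spectral power, but MRI is not the sole source. Connectivity of superficial cortex near the coil would also be less affected.

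Nor is bias between arms shown. Allocation is randomised 1:1, and outcome assessment, data collection and analysis are masked. Repositioning should affect both arms alike and mainly add noise.

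What survives is narrower: uneven coverage and added variability, from a specification that nothing else in the article repairs.

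**Conclusion.** The point holds in a limited form. Taken literally, the MRI section specifies a receive coil unsuited to uniform whole-brain T1, DTI and BOLD measurement. The consequences are lower and uneven sensitivity away from the coil, of the size computed above, and extra noise in within-patient change across four imaging visits.

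That steep fall-off occurs rests on the physics of a single loop. Its size rests on assumed radii, depths and placement, so the figures illustrate scale and do not estimate this scanner's performance.

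The correction is worth making because connectivity is a named secondary endpoint and part of the mechanistic aim. It does not threaten the motor-function outcomes or the sample size.

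**What to change.** In the MRI section, replace the circular surface coil with the scanner's multi-channel whole-head receive coil, stating type, channels and coverage. If a head array is already in use, correct the wording to say so. Add that the same coil and the same intensity normalisation apply to every patient and every visit.

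If any scan was truly acquired with a single surface coil, check it for coverage and signal-to-noise. Leave it out of the volumetric and connectivity analyses only if it fails, by a rule applied blind to arm. Automatic exclusion is not warranted, since an acute baseline scan cannot be repeated later.

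The cost is about one line of text, plus a short quality rule if it is needed. A few early scans may be lost; the Trial status section reports 2 patients included at the time of writing. The change assumes that the site has a head coil for its 3-T scanner, which the article does not confirm.

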### Outcomes {12}

Pre-intervention (− t1), 2 weeks post-intervention retention (T2), 3 months (T3), and post-intervention 6 months follow-up (T4), cranial MRI scans (T1, T2, DWI, DTI, BOLD) and EEG will be employed to detect changes in neural network connectivity, Fugl-Meyer Assessment (FMA) and Brunnstrom Limb Function Recovery Scale will be used to assess motor function, transcranial magnetic stimulation (TMS) will be used to detect neurophysiological biomarkers including MEPs and CMCT, CT perfusion (CTP) will be employed to detect cerebral blood flow, and peripheral blood samples will be collected for RNA sequencing.

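### The MRI section labels DTI-derived indices as the number and direction of nerve fibre bundles and frames them as before-after change from an acute-stroke baseline, which cannot by itself show rewiring

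*Protocol article*

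**What the plan says.** The section on functional connectivity by MRI (secondary outcomes) combines "multimodal imaging data, including T1, DTI, and BOLD functional MRI". It states that "we can compare alterations in brain fiber connectivity patterns and changes in brain functional regions before and after treatment", and that the approach makes it possible to visualise and quantify, among other things, "alterations in the number of nerve fiber bundles, changes in the direction of nerve fiber bundle pathways". DTI is the only diffusion sequence named there. The same section also lists grey matter density, cortical thickness, subcortical volumes and functional connectivity.

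The timing comes from two other places. The inclusion criteria require "Onset of symptoms within 1 week", so the pre-intervention scan is an acute one. Outcomes {12} says that "cranial MRI scans (T1, T2, DWI, DTI, BOLD) and EEG will be employed to detect changes in neural network connectivity", before the intervention and at 2 weeks, 3 months and 6 months.

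The Discussion gives the intended use, which is to "unravel the relationship between gamma oscillations and the remodeling of the brain’s neural networks". It also says that "endogenous neural repair mechanisms are initiated within hours after a stroke occurs, reaching their peak at around 10 weeks", with a plateau after 3 months.

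On design, the abstract and Trial design {8} describe 1:1 randomisation to concurrent arms and a comparison between the groups. Statistical methods {20a} tests the difference between the two groups by Student's t test or a rank test.

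**The concern.** There are two separate problems.

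**The label.** A number of bundles obtained from DTI can only come from reconstructed paths. How many there are depends on reconstruction choices and on local anisotropy as well as on anatomy. DTI does estimate the local principal direction of diffusion, but a change in that estimate near an evolving infarct is not evidence that a pathway has moved. The article states this readout as something that is quantified. It is a positive statement of what is measured, not a pipeline detail left to another document.

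**The contrast.** The MRI section names before versus after treatment. From a baseline within a week of infarction, swelling resolves, the tract below the lesion may degenerate and spontaneous repair proceeds, whatever the treatment. Any of these can move a diffusion index.

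At stake is the mechanistic conclusion. A reader of the results could be told that stimulation produced more, or redirected, fibre bundles when the data show only a changed diffusion index.

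**Working it through.** **1. The plan's own figure.** Sample size {14} gives an effect size of 0.995, power 0.95 and error probability 0.05. A two-sided two-sample t test (noncentral t) needs 27.25, so 28 per group, as stated (power 0.955 at 28). A one-sided test would need 22.57, so 23. For attrition, 28 × 1.10 = 30.8, so 31 per group and 62 in total. The figure reproduces. It was set on the upper-extremity Fugl-Meyer score and does not bear on the DTI readout; it only supplies the 28 per arm used below.

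**2. What a shared time course does to each contrast.**
- Inputs: 28 per arm (Sample size {14}); no treatment effect; the same mean change S in both arms, in units of the SD of change; 20,000 simulated trials; two-sided 5% tests.
- The values of S are assumptions. The article gives no figure for the effect of lesion evolution on any DTI measure.
- Before-after test in one arm: one-sample t test of change against 0.
- Between-arm test: two-sample t test of change.

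| Assumed shift S (SD) | Before-after in one arm, share significant | Between arms, share significant |
|---|---|---|
| 0 | 5.1% | 4.9% |
| 0.5 | 72% | 5.0% |
| 1.0 | 99.9% | 5.4% |

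The one-arm result follows from its noncentrality, S × √28. This is 0.5 × 5.29 = 2.65 at S = 0.5 and 5.29 at S = 1.0. In the between-arm contrast S − S = 0, so the error rate stays near its nominal value.

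**3. What the between-arm test does not settle.** Suppose the arms truly differ in the DTI index. Two explanations fit equally well: new or rerouted connections, or faster resolution of injury in one arm. Randomisation makes the difference attributable to allocation. It does not say which of the two the index has recorded. The Discussion's own account of endogenous repair over the same months makes the second explanation a live one.

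**The case against.** **A reader might infer that clearing oedema will be reported as rewiring.** The documents do not support this. The arms are concurrent and randomised, the planned test is between groups, and outcome assessment is blinded under Plans for assessment {18a}. A shift common to both arms cancels on average, as the table shows. Nowhere does the article say that patients' results will be reported as more or redirected fibres. The Discussion sentence "The underlying mechanism involves the restructuring of" the neural network follows directly on work in mice and is not an inference from this trial's DTI.

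**A reader might say that DTI measures neither quantity.** That is too broad for direction, since local diffusion direction is estimated. Only its reading as a rerouted pathway is in doubt.

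**A reader might argue that anisotropy is the more sensitive measure.** If repeat error (CV) is assumed to be 10 to 40% for counts and 2 to 4% for anisotropy, the smallest detectable arm difference at 28 per arm and 80% power is 0.762 × √2 × CV. That gives 10.8 to 43.1% for counts and 2.2 to 4.3% for anisotropy. The CVs are not in the documents, between-patient variation in change is left out, and the expected signal in each measure is unknown. These figures do not rank the two measures.

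**Other objections that stand.** The readout is one of several secondary imaging measures, and the primary motor outcomes are untouched. Seeding, thresholds and similar details may sit in a fuller document, so their absence here is no fault. An anisotropy ratio below the lesion also changes as the tract degenerates, and it answers a narrower question than a whole-brain connectome. It should therefore not replace that analysis.

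None of this removes the label or the before-after contrast, both of which the article states outright.

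**Conclusion.** The point holds as one of labelling, framing and interpretation in a secondary outcome. The article presents diffusion or tractography indices as the number and direction of fibre bundles, and names a before-after comparison from a baseline within 1 week of stroke. Change within a group mixes lesion evolution and spontaneous recovery with remodelling. Even a true difference between arms could reflect faster resolution of injury and not new or rerouted fibres. The randomised comparison keeps its error rate.

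The size of any lesion-evolution effect cannot be taken from the documents. The 72% and 99.9% false-positive rates for a one-arm reading depend on the assumed shifts of 0.5 and 1.0 SD and on the same mean change in both arms. That a DTI-derived number is not a fibre count is general methodological reasoning and needs no figure. The change is worth making because it is cheap and limits an unsupported mechanistic claim. It is not a threat to the trial's main result.

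**What to change.** 1. In the MRI section, call these quantities tractography indices. Report number and course descriptively, and do not describe them as fibre counts or rerouted pathways.
2. Replace the before-after contrast as the basis for structural inference. Use the difference between arms at follow-up, with the baseline value of the same measure as covariate. Within-group change may be shown but not interpreted as a treatment effect.
3. Add, from the same DTI, the ipsilesional/contralesional ratio of fractional anisotropy in an atlas-defined corticospinal tract region below the lesion. Analyse it in the same way and present it as a supporting measure of tract integrity, not of rewiring. Keep the connectome analysis.
4. State in the interpretation that a difference between arms in a DTI index is compatible with faster resolution of injury as well as with remodelling.

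The cost is a change of wording and one extra analysis, with no new scans, plus a more modest mechanistic claim. Trial status reports that inclusion has begun, so the addition should be recorded as a dated amendment.
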